**15-3 Statistical Analysis**

(1) Methods: One side, Two sample student t-test, Chi-square test, Fisher’s exact test

(2) Main analysis: ITT analysis

(3) Additional analysis: PP analysis

(4) Statistical power: 80%

* When performing the statistics for effectiveness evaluation, the information of subject who stopped to participate in or was dropped out from clinical trial is excluded from the compliance group (per protocol group) and is dealt as a missing value when the subject is assigned to the analysis group according to assignment table.

(5) General Principals of statistical analyses

The subject data of this study were analyzed through ITT (Intention to Treat) analysis and PP (Per Protocol) analysis.

In the ITT analysis, all the data obtained from the subjects who used the investigational device at least once after they were randomly assigned to the group were used. The above-mentioned subject’s information is excluded from the analysis for primary and secondary the missing value at the primary and secondary is discovered.

In the PP analysis, ITT analysis was data obtained from the subjects who completed the clinical trial according to the protocol were included. And the above-mentioned subject’s safety endpoint shall be included in ITT group. The value of subject which is out of clinical trial’s policy critically and may affect the efficacy evaluation (Exclusion criteria 2. The subject who is diagnosed as a breast cancer, absent on visit 1 and 2(each), assigned to the incorrect group, and experiences the severe adverse events during the clinical trial) will be included in the ITT group analysis with being excluded from the PP group analysis.

The efficacy evaluation was conducted using The efficacy evaluation was conducted using the ITT and PP analysis as a main method, while the PP analysis was used as an auxiliary method when the analysis results were inconsistent. The results of both analyses were compared. Demographical evaluation and safety evaluation were basically analyzed through the ITT analysis.

(6) Demographical Data

After calculating the descriptive statistics (Frequency, standard deviation, minimum value, maximum value, and percentage ratio) for the demographic and medical factors, the Independent t-test and Wilcoxon’s rank sum test shall be applied for continuous data between two groups while the Chi-square test and Fisher’s exact test shall be applied for categorical data between two groups to compare and exam the significance of descriptive statistics

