**8-3 The target enrollment number of subject and the grounds of estimation [28]**

This clinical trial is to evaluate the efficacy of Guardix SG, anti-adhesive agent composed of alginate and poloxamer in the range of motion of patient’s shoulder joint who is scheduled to undergo the modified radical mastectomy or breast preservation surgery and the axillary lymph node dissection.

According to the related literature, over 10 degree-difference in the ROM considered to be significant clinically [17] and over 10 degree-difference between the experimental group and the control in the ROM is considered to be significant. Therefore, we estimate the 192 persons(total) as a target enrollment number by assigning 96 subjects for each group in consideration of the drop-out rate of 10% under the precision degree of 0.025, power of 90%, and standard deviation of 10 [25] using Pass software.

* The rationale for our study is as follows.

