**H_0_ : D ≤ 10 H_1_ : D〉10 (D=Experimental group(EG) ROM Mean – Control group(CG) ROM Mean)**

* Basis of Calculation: Assumptions for estimating the effective subject number.

① Significance level α = 0.025

② The EG estimation number is 1 time that of CG.

③ Type 2 error (β) is 0.1, and statistical power 90% is maintained.

④ The difference in the average value between two groups: 10 degree.

[figure not shown]

[figure not shown]

[figure not shown]

| Power | N1/N2 | Equivalence Margin  (E) | Actual  Difference  (D) | Significance  Level  (Alpha) | Beta | Standard  Deviation1  (SD1) | Standard  Deviation2  (SD2) |
| --- | --- | --- | --- | --- | --- | --- | --- |
| 0.90022 | 23/23 | 5 | 10 | 0.025 | 0.09978 | 5 | 5 |
| 0.80044 | 17/17 | 5 | 10 | 0.025 | 0.19956 | 5 | 5 |
| 0.90004 | 86/86 | 5 | 10 | 0.025 | 0.09996 | 10 | 10 |
| 0.80003 | 64/64 | 5 | 10 | 0.025 | 0.19997 | 10 | 10 |
| 0.90022 | 191/191 | 5 | 10 | 0.025 | 0.09978 | 15 | 15 |
| 0.80044 | 143/143 | 5 | 10 | 0.025 | 0.19956 | 15 | 15 |
| 0.91250 | 23/23 | 10 | 15 | 0.025 | 0.08750 | 5 | 5 |
| 0.80704 | 17/17 | 10 | 15 | 0.025 | 0.19296 | 5 | 5 |
| 0.90323 | 86/86 | 10 | 15 | 0.025 | 0.09677 | 10 | 10 |
| 0.80146 | 64/64 | 10 | 15 | 0.025 | 0.19854 | 10 | 10 |
| 0.90022 | 191/191 | 10 | 15 | 0.025 | 0.09978 | 15 | 15 |
| 0.80044 | 143/143 | 10 | 15 | 0.025 | 0.19956 | 15 | 15 |

Suppose that the 10% subject is dropped out in the middle of trial, the necessary total subject is 192 persons composing of 96 persons for the experimental group and 96 persons for the control.

| Target subject number | EG | CG | In total subject number |
| --- | --- | --- | --- |
| Subject number for final efficacy evaluation | 86 | 86 | 172 |
| Subject number in consideration of drop-out rate (10%) | 96 | 96 | 192 |

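### Section 15-3 gives the trial's power as 80%, but section 8-3 sizes the same trial for 90%, and the adopted 86 per arm matches only the 90%

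*Protocol*

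**What the plan says.** Section 8-3 (target enrolment and its grounds) gives 90% power twice. The text cites "power of 90%, and standard deviation of 10 [25] using Pass software". The list of assumptions says "Type 2 error (β) is 0.1, and statistical power 90% is maintained", next to "Significance level α = 0.025". The section's table of scenarios has rows for both 90% and 80% power at SDs of 5, 10 and 15. Only the 90% result at SD 10 is carried into the target-number table: "Subject number for final efficacy evaluation | 86 | 86 | 172", rising to 96 per arm and 192 in total for 10% dropout.

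Section 15-3 (Statistical Analysis) has a short list of settings for the whole trial: the tests, the ITT main analysis, the PP additional analysis and then "4) Statistical power: 80" per cent. Nothing ties that figure to a secondary endpoint, to the per-protocol set or to a sensitivity scenario, and it is not worded as a minimum.

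**The concern.** One trial with one primary comparison has two stated powers. Either the 80% is a slip, perhaps from an unselected table row, or the sample-size section was not brought into line with a decision to design at 80%. The protocol does not say which.

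The planned power matters when the evaluable number falls short and someone must judge whether it is still enough. It matters again when a result misses the criterion and has to be read against the planned type II error. A shortfall is possible here. Section 13-5 (4) says dropouts are not replaced, and section 15-3 (5) appears to leave subjects with missing efficacy values out of the efficacy analyses. On the inputs of section 8-3, 90% power needs 86 evaluable per arm and 80% needs 64. A trial ending up to 22 per arm short could therefore be described as adequately powered by citing section 15-3.

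**Working it through.** **Inputs, all from the protocol**
- One-sided two-sample t-test (section 15-3: "1) Methods: One side, Two sample student t-test, Chi-square test, Fisher’s exact test").
- Alpha 0.025, SD 10 in both arms, 1:1 allocation, 10% dropout (section 8-3).
- True difference minus margin = 5 degrees. Every row of the section 8-3 table has this gap, as margin 5 with difference 10 or margin 10 with difference 15.

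**Formula.** With n per arm and gap d, the noncentrality is λ = d / (SD × √(2/n)) on 2n − 2 degrees of freedom. Power is the probability that a noncentral t with parameter λ exceeds the 0.975 quantile of the central t. Dropout inflation is n / (1 − 0.10), rounded up.

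**Step 1: reproduce the adopted size at 90%**
- n = 86: λ = 5 / (10 × √(2/86)) = 5 / 1.525 = 3.279; critical value 1.974; power 0.90323.
- This equals the printed table entry for 86/86 with margin 10 and difference 15.
- n = 85 gives 0.8999, so 86 is the smallest n that reaches 90%.
- Dropout: 86 / 0.9 = 95.6, so 96 per arm and 192 in total, as stated.

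**Step 2: the same inputs at the 80% of section 15-3**
- n = 64: λ = 5 / (10 × √(2/64)) = 5 / 1.768 = 2.828; critical value 1.979; power 0.80146.
- This equals the printed entry for 64/64 with margin 10 and difference 15.
- n = 63 gives 0.795, so 64 is the smallest n that reaches 80%.
- Dropout: 64 / 0.9 = 71.1, so 72 per arm and 144 in total.

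The rows with margin 5 and difference 10 print 0.90004 and 0.80003 for the same 86 and 64 per arm. The last digits differ from the recomputation, but the sample sizes are the same.

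**Step 3: could 80% describe the adopted 86 per arm?**

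| Variant at n = 86, SD 10, gap 5 | Power |
|---|---|
| t-test, one-sided 0.025 | 90.3% |
| Normal approximation, one-sided 0.025 | 90.6% |
| t-test, one-sided 0.05 | 94.7% |
| Normal approximation, one-sided 0.05 | 94.9% |

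None of these comes near 80%. To get 80% at 86 per arm with one-sided 0.025, the SD would have to be about 11.6 (gap 5), or the gap about 4.3 degrees (SD 10). The protocol states neither.

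**Size of the discrepancy.** 86 − 64 = 22 evaluable per arm; 192 − 144 = 48 patients enrolled; type II error 10% against 20%.

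**The case against.** The strongest reply is that nothing in the trial depends on the 80%. The enrolment target of 192 and the evaluable target of 86 per arm are stated explicitly, and the protocol never mentions 144. Section 15-3 gives no SD, margin, difference or N of its own, so an 80% design exists only by borrowing the inputs of the section that says 90%. The success rule in section 15-1 is a lower confidence limit above 10 degrees, and power plays no part in it. The protocol describes no interim analysis, sample-size re-estimation or stopping rule that uses power. On this view the point is a labelling inconsistency.

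Much of that stands. The planned enrolment is not in doubt, the trial is not shown to be underpowered, and no test or estimate changes. It does not remove the contradiction, because a stated design power should describe the adopted design and 80% does not. Reading 80% as a floor fails on the wording: section 15-3 gives it as the value, and section 8-3 says 90% is maintained.

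A second reply is that the 90% is itself conditional. Section 8-3 lists "The difference in the average value between two groups: 10 degree" beside a null hypothesis of D ≤ 10. Read literally, that puts the true difference on the margin and makes power equal to alpha, 2.5%, at any N. This is true and needs its own correction. The figures of 90.3%, 80.1%, 192 and 144 all rest on the 5-degree gap in the table rows. Correcting that assumption would still leave 80% in one section and 90% in the other.

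**Conclusion.** The concern holds. Sections 8-3 and 15-3 state different powers for the same trial. On the protocol's own inputs the adopted 86 evaluable per arm gives 90.3%, so the 80% in section 15-3 (4) is the entry that does not fit the design. The two figures correspond to 86 and 64 evaluable per arm, or 192 and 144 enrolled, and to a type II error of 10% and 20%. These sizes assume SD 10, one-sided alpha 0.025, a true difference 5 degrees above the margin and 10% dropout. The disagreement between the two stated powers depends on none of these. The consequence lies in how a shortfall or a missed criterion would be interpreted. The planned enrolment is unaffected. It should be corrected before results are known.

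**What to change.** In section 15-3 (4), change the stated power to 90% and refer to section 8-3 for its basis: one-sided alpha 0.025, SD 10, 86 evaluable per arm, and the margin and true difference of the table row actually used. That last item must wait until section 8-3 no longer lists a difference equal to the margin in its null hypothesis.

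If the sponsor did intend 80%, section 8-3 must change instead, to the 64/64 row and 72 per arm after dropout. Either way only one power should remain in the protocol.

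Confirming 90% costs one line of wording, with no added patients or procedures, and the total stays at 192.

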**10.2 Comparator device**

The Comparator device referred as an inactive control isn’t used in this clinical trial.

[Currently, it is uncommon to apply the anti-adhesive agent onto the surgical site of patient who underwent the modified radical mastectomy or breast preservation surgery and the axillary lymph node dissection and it is safe to apply nothing to the surgical site. Therefore, we couldn’t find the reference medical device and didn’t assigned any medical device as the control.]

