**10.3 Methods of Clinical Trial**

(1) Clinical Trial Design

The eligibility evaluation is conducted with the subject who underwent the modified radical mastectomy or breast preservation surgery and the axillary lymph node dissection at Asan medical center and signed at the consent form voluntarily subsequent to the screening test. The subject who isn’t included in the exclusion criteria visits the hospital on the operation day and undergoes the modified radical mastectomy or breast preservation surgery and the axillary lymph node dissection. Then, the subject is assigned to the investigational group or control according to the random assignment slip.

 EG: Guardix SG

 CG: Not applicable

That means the investigational device will be or won’t be applied onto the surgical site of subject depending on her group. Since the investigational device is applied inside of subject in the middle of surgery under anesthetic, the subject is unaware of treatment’s detail.

The related tests will be performed on the 7th, 3, 6 and 12 months subsequent to the surgery. In addition, the double-blind policy is maintained since the application of investigational device is performed by the expert who has a medical expertise and technique on the surgery and the application of investigational device, and the evaluator couldn’t know about the rule of random assignment and the allocation of subject to the group since the evaluator isn’t involved to the application of investigational device.

(2) Random Assignment of Subjects

In this clinical trial, random assignment was used to reduce bias that could be involved in the assignment of EG and CG, and to enhance the effects of comparison. To compare the precise difference in the range of motion of patient who underwent the partial mastectomy or total mastectomy, the subjects are assigned to each group randomly in similar proportion.

Our random assignment method is the block random assignment performed after generating random numbers (upto 4 places of decimals) for each subject using Excel’s random function (RAND). The sealed assignment slip is distributed to the subject. The sponsor of clinical trial provides the blinded slip which the investigational group or control is written down according to the randomly assigned subject table.

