**13-3. Withdrawal**

Registration means a random assignment (receipt of subject number) of subjects who participated in this clinical trial. Dropped out means a subject who was applied with the investigational medical device at least once, but he/she could not complete the clinical trial process due to any reason.

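### The ITT set, the main analysis, is conditioned on device use although controls get no device; in practice it can drop untreated patients from the device arm only, and the dropout and per-protocol rules need matching corrections

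*Protocol*

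**What the plan says.** Protocol 15-3 (2) states "Main analysis: ITT analysis", and 15-3 (3) makes per-protocol (PP) additional. Section 15-3 (5) then describes the ITT set as "all the data obtained from the subjects who used the investigational device at least once after they were randomly assigned". Demographic and safety evaluations are also based mainly on ITT.

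The control arm has no device. Section 10.2 says "The Comparator device referred as an inactive control isn’t used in this clinical trial", and the arm listing in 10.3 (1) reads "CG: Not applicable".

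Section 13-3 defines dropout in similar terms: "Dropped out means a subject who was applied with the investigational medical device at least once".

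For the PP set, 15-3 (5) lists grounds for exclusion. One is that a subject "experiences the severe adverse events during the clinical trial"; such a subject is kept in ITT. Another is labelled exclusion criterion 2 and described as a breast cancer diagnosis.

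On the roles of the two sets, 15-3 (5) says efficacy was evaluated "using the ITT and PP analysis as a main method, while the PP analysis was used as an auxiliary method" when the results disagree.

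**The concern.** A randomised comparison is protected when membership of the main set depends only on having been randomised. Here it depends on an event after randomisation that only one arm can experience. Either the rule cannot be applied to controls, or it works on the device arm alone. In the second case the main superiority comparison could set a selected device arm against an unselected control arm.

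The dropout definition has the same one-arm condition, and the PP set is filtered on an outcome that follows randomisation. These are rules the protocol states, so they are not details that it leaves to a statistical analysis plan.

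**Working it through.** **1. The planned numbers.** Section 8-3 plans 86 evaluable subjects per arm, with SD 10, one-sided alpha 0.025, margin 10 and difference 15, so a gap of 5 degrees. A noncentral t calculation with 86 per arm gives power 0.9032, matching the tabulated 0.90323. With 10% dropout, 86 / (1 − 0.10) = 95.6, rounded up to 96 per arm and 192 in total. The figures reproduce, and they need 86 evaluable controls.

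**2. Who enters ITT under each reading.** Let u be the number randomised to the device but not given it.

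| Reading of 15-3 (5) | Device arm | Control arm |
| --- | --- | --- |
| Word for word | 96 − u | 0 |
| Condition applied to the device arm only | 96 − u | 96 |
| All randomised, as assigned | 96 | 96 |

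The first row cannot be intended. Sections 15-1 and 15-2 prescribe between-group tests, and a note in 15-3 allocates subjects to analysis groups by the assignment table. The second row is the workable reading of the present text.

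**3. Effect of the second row.** Let q = u / 96, and let the mean change in range of motion of the removed patients lie d degrees below that of the retained ones. The full-arm mean is the retained mean minus q × d, so removal shifts the device-arm mean by q × d. One patient is 1/96 = 1.04% of the arm. The protocol gives neither u nor d, and d may have either sign, so no bias in degrees can be stated.

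**4. Can u exceed zero?** Yes. Section 12-3 lists an infected or contaminated surgical site as a contraindication, and 12-1 bars use when the container or package is damaged. The first ground is related to the patient's condition, so such losses need not be random. A control with the same site would stay in the analysis.

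**5. Dropout.** Section 15-2 (1) compares by group the rate of adverse events that caused dropout. Under the 13-3 wording no control can be a dropout, so the control rate would be zero by definition.

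**6. Severe adverse events and PP.** Section 12-5 lists reduced shoulder movement among the expected events of surgery, so this exclusion can overlap with the primary endpoint. Suppose fractions pE and pC are excluded from the device and control arms, and their motion is D degrees below the rest of their arm. The PP difference then shifts by (pE − pC) × D. The protocol gives none of these inputs. On assumed values:

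- 5% against 2%, D = 10: 0.03 × 10 = +0.3 degrees
- 10% against 2%, D = 30: 0.08 × 30 = +2.4 degrees
- the same rates with the arms exchanged: −0.3 and −2.4 degrees
- equal rates and equal impairment: 0

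The sign depends on which arm has more severe events.

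**7. Eligibility reference.** Exclusion criterion 2 in 8-2 is Stage IV disease. Breast cancer diagnosis is inclusion criterion 2 in 8-1. The PP list combines the number of one with the content of the other.

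**The case against.** The best defence is that this is a translated protocol whose intent is clear. Controls are planned for, compared and allocated by the assignment table. The device is applied once, at the operation where assignment takes place, so non-use may be rare. The rules in 13, 13-4 and 13-5 speak of subjects without a device condition. No PP set preserves randomisation, and here PP is additional.

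Much of this stands, and it rules out several stronger readings that a reader might infer:

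- **That the main analysis has no controls.** The wording says so, but the rest of the protocol contradicts it.
- **That PP is empty because every patient has breast cancer.** The entry sits among serious departures from the protocol, and 13-4 (3) uses the same idea for inclusion violations. It reads as a garbled eligibility-violation rule.
- **That PP favours the device.** The exclusion applies to both arms. If the device works, more controls with poor motion could be removed, which would bias PP against it.
- **That the sponsor may choose the better of two main results.** The full sentence makes PP auxiliary when the sets disagree, and 15-3 (2) and (3) already rank them.
- **That the main analysis carries a bias of known size.** Any figure in degrees needs assumed rates and gaps, and must not pool non-use, which affects ITT, with severe events, which affect PP only.

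What the defence does not answer is how controls enter ITT, or why an untreated device-arm patient should leave it. No sentence in the protocol says.

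**Conclusion.** The ITT definition is wrong as written and must be corrected, because it governs the main analysis. Its practical consequence is an asymmetric exclusion after randomisation, limited to device-arm patients who do not receive the device. Its size and direction are unknown, and it is zero if every such patient is treated. This rests on reading the protocol as intending to include controls, which its sample size and planned tests support.

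The dropout definition has the same defect. The severe-event exclusion is a real but secondary weakness, since those patients stay in ITT and the direction of any PP bias is indeterminate. The criterion reference and the sentence on main methods are drafting errors.

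**What to change.** - **15-3 (5), ITT:** define it as all randomised subjects, analysed in the arm assigned, whether or not the device was applied.
- **13-3:** define dropout identically in both arms, as randomised and not completing visit 5.
- **15-3 (5), PP:** remove severe adverse events from the exclusions.
- **15-3 (5), eligibility entry:** correct it to mean violation of the intended criterion, with the right number. Do not delete it, since a genuine eligibility violation is a legitimate PP exclusion.
- **15-3 (5), roles:** reword the sentence on main methods to agree with 15-3 (2) and (3), with ITT primary and PP supportive.

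The cost is wording in two sections, with no new data and no change to the 192 subjects. One limit should be noted: 15-3 (5) also leaves subjects with missing primary or secondary values out of those analyses. Redefining ITT does not change that rule, which needs its own consideration.

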**13. Procedure of drop-out and withdrawal**

When the subject stops to participating in or is dropped out from the clinical trial, the result collected from the discontinued date until the time her discontinuation is handled as a withdrawal will be reviewed during the final evaluation if the result’s item can be used for evaluation.

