**13-4. Withdrawal Criteria**

(1) The clinical trial can be withdrawn if the required tests cannot be conducted due to subject conditions or other reasons.

(2) The clinical trial can be withdrawn if subjects show serious AE, adverse device effect (ADE), or serious AE (SAE), which make it difficult to continue with the clinical trial.

(3) The clinical trial can be withdrawn if a serious offence of the protocol develops.

- The clinical trial can be discontinued due to the offence of the inclusion criteria, which can affect the efficacy evaluation.

(4) The clinical trial can be withdrawn if the subjects or legally authorized representatives want discontinuation through withdrawal of the written consent.

(5) The clinical trial can be withdrawn if subjects are not followed up.

(6) The clinical trial can be withdrawn if investigators determine it should be

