**13-5. Process of Withdrawal**

(1) Dropout cases must be appropriately managed and treated, and the development must be observed and recorded. The reason of withdrawal must be recorded in the CRF.

(2) All the test results up to the time of withdrawal, the date, reasons, treatments and progress at the time of withdrawal must be recorded in the CRF.

(3) If subjects do not show up for a visit, mail, interview, and phone calls can be used to investigate the reasons and progress, and the results are recorded in the CRF.

(4) The dropout subjects are not replaced with new subjects.

(5) If subjects withdraw in the middle of the clinical trial, they are not required to explain the reason, but investigators must try to confirm the reason upon considering the subject rights.

(6) If there is an outcome of efficacy and safety evaluation (such as AE and concomitant medication) at the time of withdrawal, it must be included in the analysis unless this distorts the validity of the clinical trial.

(7) The result of pregnant subject can be collected only for ethical purpose and the observation on that subject will be continued even after the drop-out.

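### The main efficacy analysis is called ITT, but an ambiguous exclusion rule removes patients with missing values, in tension with the protocol's own rules on using data from withdrawn patients

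*Protocol*

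**What the plan says.** Section 15-3 gives several instructions that bear on patients with missing data.

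- The main analysis is intention to treat: "2) Main analysis: ITT analysis".
- Section 15-3 (5) describes that set as follows: "all the data obtained from the subjects who used the investigational device at least once after they were randomly assigned to the group were used".
- Its next sentence says that the subject's "information is excluded from the analysis for primary and secondary the missing value at the primary and secondary is discovered".
- The starred note after 15-3 (4) says that the information of a subject who stopped or dropped out is left out of the per-protocol group and "is dealt as a missing value when the subject is assigned to the analysis group according to assignment table".
- For the per-protocol analysis, "data obtained from the subjects who completed the clinical trial according to the protocol were included".

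Section 13 treats the same patients differently. The opening paragraph says that results of a discontinued subject "will be reviewed during the final evaluation if the result’s item can be used for evaluation". Section 13-5 (6) says of efficacy and safety outcomes available at withdrawal that "it must be included in the analysis unless this distorts the validity of the clinical trial".

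Shoulder motion is measured before surgery and at 3, 6 and 12 months. Section 15-1 (2) plans one-sided two-sample t-tests for each motion and each period. It declares superiority when the lower confidence limit exceeds 10 degrees. Section 8-3 counts 86 per arm for the final efficacy evaluation, out of 96 per arm enrolled.

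**The concern.** An analysis described as using all data from randomised patients should not have, in the next sentence, a rule that takes patients out when a value is missing. The protocol names no other method that would keep them in, and it says the opposite in section 13-5 (6). A statistician following 15-3 and one following 13-5 could analyse different patients.

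What is at stake is the randomised comparison. Section 12-5 lists reduced shoulder movement among the expected events after surgery, and section 15-2 plans to report adverse events that caused dropout. A link between dropout and the primary outcome is therefore plausible, although the protocol does not establish one. If dropout also differs between arms, the patients who remain are no longer a fair comparison. Measurements already taken may be discarded as well.

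**Working it through.** **1. The plan's own numbers.** Two rows of the table in section 8-3 give 86 per arm with SD 10 and 90% power at one-sided 0.025: margin 5 with difference 10, and margin 10 with difference 15. Both leave a 5-degree gap between margin and assumed difference. With gap 5, SD 10 and 86 per arm, the noncentral t gives power 0.9032, which matches the table's 0.90323 for the 10-degree margin. Allowing for 10% dropout, 86 / 0.9 = 95.6, rounded up to 96 per arm, or 192 in total. So 192 − 172 = 20 randomised patients are expected to be missing from the final efficacy evaluation.

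**2. Two readings of the exclusion sentence.**

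- *Reading A: any missing value removes the patient from all visits.* A patient with 3- and 6-month values but no 12-month value is lost from every test. This conflicts with 13-5 (6) and section 13, and with the statement in 15-3 (5) that all data are used. If a share m of values is missing independently at each of three visits, the share of patients lost is 1 − (1 − m)³. This gives 8.7% for m = 3%, 14.3% for m = 5% and 27.1% for m = 10% (assumed values). The last two exceed the planned 10%.
- *Reading B: exclusion applies separately to each endpoint and visit.* Each t-test uses whoever has a value at that visit. A dropout's 3-month value counts at 3 months, so 13-5 (6) can be met. At 12 months the patient is absent, and the earlier values are not used to inform that comparison.

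**3. Size of a possible bias.** Let d1 and d0 be the dropout proportions on device and control. Let g be the amount by which lost patients have worse motion than those retained, taken as equal in both arms. An arm's retained mean exceeds its full mean by d × g, so

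bias in the difference = (d1 − d0) × g.

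The documents give no values for d1, d0 or g separately. The values below are assumptions, chosen so that the average dropout is the planned 10%. For type I error, the true difference is set at the 10-degree margin, with SD 10 and 96 randomised per arm. At 15% v 5% dropout, 81.6 and 91.2 remain, so SE = 10 × √(1/81.6 + 1/91.2) = 1.52. One-sided type I error = 1 − Φ(1.96 − bias/SE).

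| Dropout, device v control | Deficit g | Bias | Type I error |
| --- | --- | --- | --- |
| 10% v 10% | 10 or 20 | 0 | 0.025 |
| 15% v 5% | 10 | 0.10 × 10 = +1.0 | about 0.10 |
| 15% v 5% | 15 | 0.10 × 15 = +1.5 | about 0.16 |
| 15% v 5% | 20 | 0.10 × 20 = +2.0 | about 0.26 |
| 5% v 15% | 10 to 20 | −1.0 to −2.0 | below 0.025; power is lost instead |

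For scale, 1.5 degrees is 1.5 / 5 = 30% of the gap on which the trial is powered.

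**The case against.** The strongest reply is that the sentence is broken text and that Reading B is at least as natural as Reading A, because sections 15-1 (2) and (3) plan a separate test for each period. Under Reading B a dropout's existing results are used where they exist, and the conflict with 13-5 (6) largely disappears. That section also has an exception for validity. This stands: the contradiction is firm only under Reading A. The exception does not rescue Reading A, because 15-3 excludes without invoking it.

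A reader might infer more than the protocol supports on three points.

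- *That the ITT analysis is simply a completers analysis, or the same as per protocol.* It is not. Section 15-3 (5) keeps patients with severe adverse events, wrong assignment or other critical violations in the ITT analysis and removes them only from per protocol. It is a missing value that takes a patient out, not the complication.
- *That the withdrawal criteria end follow-up after an adverse event.* Section 13-4 (2) reads "The clinical trial can be withdrawn if subjects show serious AE, adverse device effect (ADE), or serious AE (SAE" and goes on to limit this to events that make continuing difficult. It permits withdrawal and does not require it. Section 13-6 leaves continuation after a violation to the investigators, and 13-5 (1) and (3) require dropouts to be observed and allow contact after missed visits.
- *That the bias favours the device.* Nothing in the protocol fixes its direction or shows that it exists. Equal dropout with equal deficit gives zero.

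It can also be said that missing-data methods belong in an analysis plan, which is not shown here. That would answer a complaint about silence, but the protocol states a rule.

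**Conclusion.** The point holds in a limited form, with moderate confidence. The protocol labels its main efficacy analysis ITT and then applies an exclusion rule that can be read in two ways. One reading contradicts sections 13 and 13-5 (6). The other gives available-case t-tests that drop patients without a value at the visit and ignore their other visits. On the plan's own figures about 20 of 192 patients are expected to be missing from the final efficacy evaluation. Under Reading B some of them would still count at earlier visits.

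The bias figures, 0 to 2.0 degrees in either direction, rest entirely on assumed dropout splits and deficits. They show what the rule would allow if dropout differed by arm and was related to motion, and they do not predict what will happen. The sample size itself reproduces and is not in question here.

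**What to change.** - Delete the exclusion sentence in 15-3 (5), and bring the starred note after 15-3 (4) into line with section 13 and 13-5 (6), so that one rule governs data from patients who leave early.
- Analyse all randomised patients as assigned, using every observed motion value at 3, 6 and 12 months in a repeated-measures model with baseline, arm, visit and arm-by-visit terms. Apply the existing criterion, lower confidence limit above 10 degrees, to the arm contrast at each visit. Use the same approach for DASH and VAS.
- Add a sensitivity analysis in which missing values are allowed to be worse than observed ones, by amounts that may differ between arms.
- Reconcile the withdrawal criteria in 13-4 with the follow-up described in 13-5, and state whether the already scheduled visits 3 to 5 are still measured in patients who leave early without withdrawing consent. No withdrawal rule is proposed here.

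The cost is protocol wording and modest extra analysis, with no new visits. The model relies on data being missing at random. By itself it would not remove a bias from loss that depends on unobserved motion, which is why the sensitivity analysis is needed. Patients with no post-baseline value still contribute nothing to the comparison.
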